#### Monitoring

The trial coordinator and lead investigators meet fortnightly to monitor adverse events, any issues relating to the trial, review recruitment and trial progress.

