## Methods/design

### Trial design

This trial is a parallel-design 2-arm, assessor- and participant-blinded randomised controlled trial. Outcomes are assessed at baseline and 24 weeks after baseline. This protocol complies with the SPIRIT guidelines [35] with reporting following both CONSORT [36–38] and TIDieR guidelines [39]. Figure 1 outlines trial phases.

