For the SMS intervention, participants receive up to five text messages weekly. Message frequency reduces over the 24-week intervention, as recommended in the literature, to lessen participant burden [44]. Message length ranges from 105 to 420 characters. Each week (weeks 1–8) to each fortnight (weeks 9–24) participants receive a message asking them to self-report the number of home exercise sessions completed in the previous week. Participants who report low adherence (≤2 exercise session/week) then receive a message prompting them to select a barrier from a predetermined list (forgot, too tired, knee hurts so can’t exercise, worried exercise is causing pain, exercise isn’t helping, boring, lack of time, life stress, and none above apply to me) which best explains why they were unable to complete their exercises as prescribed (three times in the previous week). Participant barrier selection then triggers a BCT message providing a suggestion tailored to help address the selected barrier. Additional file 1 lists the BCTs used to address each barrier. Program automation is designed to prevent the same message being sent if the same barrier is selected more than once. Participants who report being adherent (≥3 exercise session/week) receive a positive reinforcement message encouraging continued completion of the home exercises three times each week with program automation ensuring a different message is received each time. Participants also receive regular motivational SMS (twice weekly initially and reducing to once fortnightly by 24-weeks) containing BCT suggestions linked to exercise facilitators. Additional file 2 lists the exercise facilitators targeted in the intervention and the BCTs which were converted into SMS to address them. Furthermore, to enhance engagement, participants receive special occasion messages (e.g. birthday, Christmas).

After randomisation, each participant is guided by a researcher through a three-message practice sequence to assist in replying to messages and are informed that they can opt out of the SMS intervention at any time by sending the word “stop” to the SMS program number. This practice session is in person at the University of Melbourne or remotely via email if the participant is unable to attend baseline assessment at the university. Participants are not restricted from taking medication or pursuing other knee interventions during the 24-weeks.

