##### Adverse events

Any problem that participants believe was caused by the advice received as part of the study and required them to seek treatment/take medications, and/or interfered with function for two or more days are recorded via questionnaire at 24 weeks.

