### Data analysis, monitoring and auditing

#### Sample size calculation

The ADHERE trial includes eligible participants exiting from the TARGET trial (*n* = 128 total initial sample for TARGET). We conservatively estimate that 102 participants (80% of the 128 TARGET enrollees) will be randomised into the ADHERE trial, and that of those 102 participants, 82 (80%) will be retained in ADHERE until week 24. With 40 participants per group, we will have 83% power to detect an effect size of 0.6 with two-sided significance level of 0.05. This assumes a correlation between baseline home exercise adherence (taken from TARGET trial final time-point) and adherence outcomes at 24 weeks of 0.4, based on data from our previous trials [53–55] and including baseline adherence in the regression model as a covariate. This calculation assumes that the effect size of interest is the same for both primary outcomes and therefore applies to both/either.

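### Adverse events are to be monitored fortnightly, but the only collection described is one 24-week questionnaire limited to problems the participant blames on study advice

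*Protocol article*

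**What the plan says.** All references are to the protocol article.

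- **Monitoring:** "The trial coordinator and lead investigators meet fortnightly to monitor adverse events", alongside recruitment, progress and other trial issues.
- **Adverse events:** an event is "Any problem that participants believe was caused by the advice received as part of the study and required them to seek treatment/take medications", or one that "interfered with function for two or more days are recorded via questionnaire at 24 weeks". It is listed among the other measures that follow the secondary outcomes. No start date for the recall period is given.
- **Trial design:** "Outcomes are assessed at baseline and 24 weeks after baseline". The Procedures section adds that follow-up is by remote online survey.
- **Sample size calculation:** of 102 participants randomised, "82 (80%) will be retained in ADHERE until week 24".
- **SMS intervention:** "participants receive up to five text messages weekly", with the frequency falling over the 24 weeks. Participants who report few sessions choose a barrier from a list that includes knee pain and worry that exercise is causing pain. The reply triggers an automated suggestion and is not described as adverse-event capture.
- **Discussion:** the control arm is described as having no contact.

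**The concern.** Two stated rules do not fit together. Oversight is to run every two weeks, but the one instrument described is completed when the participant's unsupervised exercise period is over. An event in someone still in follow-up has no described way of reaching the meeting, and an event in someone who leaves early has no described way of being recorded at all.

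The definition raises a second problem. It filters events by whether the participant blames the study's advice, and continuing advice is what separates the arms. The same knee flare could be reported more readily, or less readily, by someone receiving regular texts.

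At stake are whether the stated safety oversight can work as described and whether the harms data can be interpreted. The adherence outcomes are not affected.

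**Working it through.** **1. The plan's retention figures.** From the Sample size calculation section:
- 0.80 × 128 = 102.4, stated as 102 randomised.
- 0.80 × 102 = 81.6, stated as 82 retained.

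Both figures reproduce.

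**2. Participants without a record.** 102 − 82 = 20, and 20/102 = 19.6%. No collection at withdrawal is described.

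**3. Timing.** At one meeting per fortnight, 24/2 = 12 meetings fall within one participant's follow-up before the questionnaire is due. As an illustration only, assume that event times are uniform over the 24 weeks and that the questionnaire is the sole source. The mean wait before recording is then 24/2 = 12 weeks, and the share of events waiting longer than one meeting interval is (24 − 2)/24 = 22/24 = 92%. The article gives no event-time distribution.

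**4. What 20 missing records do to an incidence estimate.** The article gives no event rate, so the number of events x among the 82 responders is assumed. The lower bound is x/102 (no events among the 20 missing). The upper bound is (x + 20)/102 (an event in all 20).

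| x (assumed) | Rate in responders, x/82 | Possible rate in all 102 |
|---|---|---|
| 4 | 4.9% | 3.9% to 23.5% |
| 8 | 9.8% | 7.8% to 27.5% |
| 16 | 19.5% | 15.7% to 35.3% |

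The width is always 20/102 = 19.6 percentage points. These are extreme bounds, not likely values.

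**5. If leaving depends on having an event.** Assume a true rate p = 0.20 and overall drop-out of 20%. Write dA and dN for drop-out with and without an event. The observed rate is p(1 − dA) / [p(1 − dA) + (1 − p)(1 − dN)].
- dA = dN = 0.20: 0.16/(0.16 + 0.64) = 20%, no distortion.
- dA = 0.40, dN = 0.15: 0.12/(0.12 + 0.68) = 15%.
- dA = 0.60, dN = 0.10: 0.08/(0.08 + 0.72) = 10%.

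If the dependence is the same in both arms, both rates are understated alike. With equal true rates, an apparent difference arises only if drop-out or attribution differs by arm. The article gives neither input.

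**6. Attribution, by comparing sections.** The item asks about "Any problem that participants believe was caused by the advice received as part of the study". The SMS arm receives messages throughout and the control arm does not, so the prompt can be read differently in the two arms. Under Randomization and blinding, participants are not told that there are two studies. The phrase can therefore also reach back to the TARGET physiotherapist's instruction, which both arms received, and this would narrow the contrast between arms. No arithmetic from the article settles the net effect.

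**The case against.** The strongest reply is that the two sections do different jobs. One defines a survey item; the other describes operational oversight. Neither says that the questionnaire is the sole source, and a condensed article may leave a route for spontaneous reports to the full protocol. That stands: sole collection is inferred from what is described, not stated. It does not remove the need for the two sections to agree on what the meetings review.

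A reader might infer that the monitoring receives nothing timely. The documents do not support that. Participants enter ADHERE as they finish TARGET, so if entry is staggered, completed questionnaires reach meetings while others are still being followed. Each nevertheless arrives only after that participant's own 24 weeks.

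A reader might also infer that the comparison of harms between arms is biased. That is not shown either. Both arms answer the same item at the same time, the Data analysis section names no adverse-event comparison, and the article gives no attribution rates.

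The attribution limit is partly offset. Medication and treatment use over the past six months, overall knee pain and the KOOS subscales are collected in both arms regardless of blame, but at 24 weeks only from those who respond.

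Finally, the 80% retention is called conservative, and loss to follow-up affects every 24-week outcome. Both points are fair. Multiple imputation, planned where more than 5% of an outcome is missing, would help little if leaving depends on the unrecorded event. That people aggravated by exercise are among those who leave is plausible but not documented.

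**Conclusion.** The point holds as a mismatch to reconcile, with one avoidable weakness in the item's wording. As described, fortnightly monitoring has no within-follow-up source for a given participant, and 20 of 102 (19.6%) would give no adverse-event record if the planned retention is met. Filtering events by belief about the study's advice puts any between-arm description of harms at risk of differential attribution, of unknown size and direction.

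The conclusion rests on the article's description being complete as to collection. If the full protocol contains a reporting route, the timing part reduces to stating it. The delay figures depend on the uniform-time assumption, and the incidence ranges on assumed event counts. A change should be made because a better method is available at little cost; the primary analysis and the sample size do not depend on it.

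**What to change.** 1. **Survey item.** At 24 weeks, first ask both arms about any new or worsened problem since ADHERE baseline that needed treatment or medication, or limited function for at least two days, whatever its cause. Ask about believed cause as a second item. The present definition can then still be tabulated as a subset.
2. **Withdrawal.** Send the same item to anyone who leaves before week 24.
3. **Monitoring section.** State what feeds the fortnightly meetings. One option is a dated log of reports that participants in both arms are invited, in identical words at ADHERE baseline, to make to the coordinator. Because the participant initiates these, the control arm stays free of outgoing contact.
4. **Reporting.** Describe the arms on the survey item. List spontaneous reports and any SMS replies separately, because the reply channel exists in one arm only.

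The cost is one sentence in the baseline instructions, a log kept by the existing coordinator, one branching item in an online survey already in use, and a minor amendment. The drawback is that more background osteoarthritis flares and unrelated events will be recorded and will need review.

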#### Dissemination plans

Findings of this trial will be presented at conferences, published in a peer-reviewed journal and a lay summary of findings provided to all participants. In addition, dissemination of findings will be through research networks including the Centre for Health, Exercise and Sports Medicine, and the National Health and Medical Research Council Centre for Research Excellence in Translational Research in Musculoskeletal Pain.

## Discussion

This RCT is investigating if a behaviour change theory-informed SMS intervention that addresses key barriers and facilitators to exercise adherence in people with knee OA, delivered once clinician involvement ceases, can improve adherence to a prescribed home-based exercise program over 24-weeks when compared to a no contact control. This study will provide insight into the effectiveness of SMS technology to promote adherence in the knee OA population and if effective will be an easily scalable, cheap and accessible intervention for people with knee OA including those in regional and remote areas.

## Data Availability

The SMS programs behaviour change message library will be available by request on a case-by-case basis at the discretion of the corresponding author.

## Abbreviations

BCT: Behaviour Change Technique
BCW: Behaviour Change Wheel
SMS: Short Messaging Service
